### Advantages

The design of this RCT encompasses numerous advantages. The main strength of our study is the *combination* of two interventions; coupling brain stimulation with group therapy may exert cumulative therapeutic effects in gesturing and functioning in schizophrenia (20). Additionally, cTBS enhances neuroplasticity in schizophrenia patients (46, 74) and thus, may facilitate SCRT training effects. Thanks to the two comparators (sham cTBS and sham SCRT) we can evaluate the therapeutic effects of both interventions on behavioral, clinical, and neural levels. Also, we may find insights to predictors of treatment outcome. Further, the RCT design allows elimination of selection bias in treatment assignment and enables blinding from assessors and participants. Moreover, by collecting detailed demographic information over time, we will be able to correct for age, gender, education and antipsychotic medication dosage. Longitudinal data allows exploration of change in our patients, and thus, gives insight on the longevity of treatment effects. For example, our design may shed light on factors that are essential for the transfer of coping strategies. Most importantly, we are running one of the very few RCT on SCRT to involve acquisition of neuroimaging data before and after intervention. We can directly compare neural alterations to potential behavioral changes after the interventions. If this study proves to be successful it has the potential to be beneficial for other psychiatric disorders, which exhibit similar socio-cognitive dysfunctions such as depression (93, 94).

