## Methods

### Aims and Hypotheses

This study’s main goal is to determine the effects of combined cTBS over rIPL and SCRT on gesture performance and social functioning in patients with schizophrenia. In addition, we aim to investigate neurocognitive, social cognitive, motor, clinical and neural effects of both interventions as secondary outcome measures. As cTBS enhances neuroplasticity and improves use of neural resources (46, 74), we expect administration of cTBS to facilitate SCRT training effects. Additionally, we hypothesize that the expected improvement of gesture performance will have positive effects on functional outcome, as both have been reported to be linked in schizophrenia (20). At the neural level, we hypothesize that the brain activity of patients will converge to the brain activity of healthy controls after both interventions, especially within the praxis network (39, 40).

This randomized controlled trial (RCT) will include three patient groups (see Figure 1). First, group A will receive real cTBS and real SCRT. Second, group B will receive sham cTBS and real SCRT. Third, group C will receive no cTBS and sham SCRT. In this study, we will also include a fourth group consisting of healthy controls, who will be assessed twice without any intervention in between. We expect the combination of cTBS and SCRT to show positive effects on both primary and secondary outcomes in patients with schizophrenia spectrum disorders. As such, we expect group A to have superior performance over group B and C in gesture performance and functional outcome after intervention (A > B > C).

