**FIGURE 1 F1:**
[figure not shown]
Study Setup. We will randomize 72 schizophrenia patients in three different groups (24 patients per group). Group A will receive real cTBS and real SCRT. Group B will receive sham cTBS and real SCRT. Group C will receive no cTBS and sham SCRT. Both sham treatments are inactive interventions that mimic as closely as possible the real treatments. Group A and B will receive 10 cTBS sessions during the first two weeks of intervention. Additionally, Group A–C will receive 16 SCRT sessions for eight weeks. Outcomes will be measured during four different time points: baseline, after cTBS (week 2), after SCRT (week 8) and follow-up (week 32). We will also include a fourth group consisting of 24 healthy controls, who will be assessed twice (baseline and week 8) without any intervention in between.

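### Group C receives no stimulation, real or sham, so the trial can isolate cTBS as an add-on but not SCRT alone, nor a fully sham-controlled combined effect

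*Protocol article*

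**What the plan says.** Aims and Hypotheses gives both active treatments to group A, and pairs active SCRT with the placebo coil in group B. Of the remaining patient arm it says: "Third, group C will receive no cTBS and sham SCRT".

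The Figure 1 legend agrees on who attends stimulation: "Group A and B will receive 10 cTBS sessions during the first two weeks of intervention". Nothing in the article gives group C a sham coil. The same legend says of the shams: "Both sham treatments are inactive interventions that mimic as closely as possible the real treatments".

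The aim is stated as: "This study’s main goal is to determine the effects of combined cTBS over rIPL and SCRT on gesture performance and social functioning". The expected order is A above B above C. Statistical Considerations and Plan specifies a repeated measures analysis of three patient groups at three main time points and names no primary pairwise contrast.

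The Discussion, under Advantages, then concludes: "Thanks to the two comparators (sham cTBS and sham SCRT) we can evaluate the therapeutic effects of both interventions". The Limitations section lists four limitations; the missing combination of sham cTBS with sham SCRT is not among them.

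**The concern.** No two arms differ only in SCRT. Going from C to B changes two things at once: sham SCRT becomes real SCRT, and ten placebo-coil sessions are added. Those sessions bring extra visits, staff contact and the expectation that goes with a device treatment. Group C has none of this.

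If attending sham stimulation moves TULIA or the functional scales at all, the shift appears inside B minus C and would be read as an SCRT effect. It also appears inside A minus C, the natural contrast for the combination because C is the only arm with neither active treatment. The Advantages sentence invites that reading, since it presents the two shams as sufficient to evaluate each intervention.

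**Working it through.** **1. The plan's own figure.** Statistical Considerations and Plan gives f = 0.15, correlation 0.75, power 0.95, alpha 0.05 and N = 72. For the group-by-time interaction with 3 groups and 3 times, assuming sphericity:

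- λ = f² × N × m / (1 − ρ) = 0.0225 × 72 × 3 / 0.25 = 19.44
- df = (3 − 1)(3 − 1) = 4 and (72 − 3)(3 − 1) = 138
- power = 0.952, and 72 is the smallest equal-arm N that reaches 0.95

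The sample size reproduces. It is not in dispute; it supplies the arm size and correlation used in step 3.

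**2. What each contrast estimates.** Define three effects:

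- T = real minus sham cTBS, given real SCRT
- S = real minus sham SCRT, given sham cTBS
- P = sham-cTBS attendance minus no stimulation, given sham SCRT

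| Contrast | Arms compared | Estimates |
|---|---|---|
| A − B | real cTBS + real SCRT vs sham cTBS + real SCRT | T |
| B − C | sham cTBS + real SCRT vs no cTBS + sham SCRT | S + P |
| A − C | real cTBS + real SCRT vs no cTBS + sham SCRT | T + S + P |

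Three arms give two independent contrasts for three unknowns. S is identified only if P = 0, an assumption the article neither states nor defends. Splitting S from P without an assumption would need an arm with sham cTBS and sham SCRT, which the trial does not have.

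**3. How much P could matter (illustration).** The documents give no value for P, so the range is assumed. Take S = 0, a positive P that persists undiminished to week 8, 24 patients per arm, correlation 0.75, and a two-sided 5% test of B − C on the baseline-to-week-8 change.

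- SD of change = √(2 × (1 − 0.75)) = 0.707 raw SD
- SE of B − C = 0.707 × √(2/24) = 0.204 SD
- noncentrality = P / 0.204

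| Assumed P (SD) | Noncentrality | Chance B − C is significant (69 df) |
|---|---|---|
| 0 | 0 | 5% |
| 0.1 | 0.49 | 8% |
| 0.2 | 0.98 | 16% |
| 0.3 | 1.47 | 31% |

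Using groups B and C alone (46 df) gives 8%, 16% and 30%.

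**4. The overall test.** If A and B share the shift P at weeks 2 and 8 and no specific effect exists, λ for the 4-df interaction is 0.43, 1.71 and 3.84 for P = 0.1, 0.2 and 0.3 SD. It then rejects 7%, 15% and 30% of the time.

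**5. Scale.** With equally spaced arms, λ = 19.44 corresponds to a step between adjacent arms of 0.39 SD if the effect is complete by week 2, or 0.45 SD at week 8 if it grows evenly. An assumed P of 0.2 SD would be about half a planned step.

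**The case against.** Much of the defence stands.

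- **cTBS is properly controlled.** A − B differs only in the coil. A reader might infer that the Advantages sentence is wrong altogether; it is not. It holds for cTBS as an add-on to real SCRT.
- **SCRT has a comparator.** Group C attends 16 sham group sessions, so group format and therapist contact are matched. What is unmatched is the stimulation visits: 10 × 17 = 170 minutes, against 16 × 90 = 1,440 minutes of group sessions in every patient arm, or about 12%.
- **No primary contrast is named.** A reader might infer that A − C is the declared main comparison. The article states the combination as its goal and plans a three-group analysis; A − C is a reasonable inference, not a stated choice.
- **Only one independent step is affected.** It is tempting to say that most of the A > B > C ordering is contaminated. The ordering has two steps, and only B > C carries P independently; A − C is their sum.
- **Direction is not established.** The documents do not show that sham sessions improve TULIA. Limitations mentions the additional stress of participation, so a negative P cannot be ruled out.
- **Rating is blinded.** Under Behavioral and Clinical Assessments, TULIA is scored from video by an independent examiner blind to group and timing. This limits rater bias. It does not remove differences in patients' expectation or contact.

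None of this separates S from P. It narrows the claim and makes the size uncertain.

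**Conclusion.** The concern holds in a limited form and should be fixed. A − B gives a sham-controlled estimate of cTBS on top of real SCRT. B − C estimates SCRT plus attendance at ten sham-cTBS sessions, and A − C estimates the whole package against sham SCRT without stimulation. The Advantages claim therefore fails for SCRT alone and for a fully sham-controlled combined effect, and Limitations does not say so.

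The identification result needs only the arm definitions. The percentages rest on assumed values of P, its persistence to week 8, S = 0 and full arms of 24; they show sensitivity and do not estimate a bias. The documents do not support saying that B − C or A − C is biased upward, only that neither can be attributed to its active components without assuming P = 0.

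**What to change.** Keep the arms; Trial Status reports 65 patients already recruited.

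1. Qualify the Advantages sentence so that it claims sham-controlled evaluation for cTBS added to real SCRT only, and add the absent sham-cTBS-with-sham-SCRT arm to Limitations.
2. Name A − B as the only contrast that supports a sham-controlled claim about a single component.
3. Report B − C as *SCRT plus sham stimulation versus sham SCRT*, and A − C as *whole package versus sham SCRT without stimulation*. Do not attribute B > C to SCRT alone.
4. Optionally, add B − C on the week-2 to week-8 change in TULIA as a supportive SCRT estimate. Stimulation ends by week 2, and at two sessions a week about 16 − 4 = 12 SCRT sessions follow. State its limits: it misses any SCRT gain reached by week 2, and it is free of P only if any sham-session effect stays constant after week 2. If a positive effect fades, SCRT is underestimated.

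Items 1 to 3 cost wording and a more modest claim for SCRT and the combination. Item 4 needs no new assessment, since TULIA is already scheduled at both visits, but the data were incomplete at the time of writing: 36 patients had finished week 8.

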**Assessments**					
Gesture tests	**X**	**X**	**X**	**X**	**X**
Clinical rating scales	**X**	**X**		**X**	**X**
Community functioning		**X**		**X**	**X**
Neuroimaging		**X**		**X**	

Secondary outcomes will include additional nonverbal communication, cognitive, clinical, and functional assessments, as well as self-reports. Nonverbal communication will be tested with the Profile of Nonverbal Sensitivity (PONS) (78) assessing nonverbal social perception, and the modified postural knowledge task (79, 80) measuring gesture perception. Together, TULIA, PKT, and PONS assess nonverbal communication, as they include the *production*, the *recognition*, and the *interpretation* of gestures. History of symptoms and medication in patients will be assessed with The Comprehensive Assessment of Symptoms and History (CASH) (81). Self-reports, clinical scales, motor scales, cognitive tests and functional assessments are listed in Table 4.

**TABLE 4 T4:** Primary and secondary outcomes.

Assessments		References
Self-reports	Brief Assessment of Gestures (BAG)	(95)
	Self-report of negative symptoms (SNS)	(96)
	The satisfaction with therapy and therapist scale-revised (STTS-R) for group psychotherapy	(97)
Psychopathology	Positive and negative syndrome scale (PANSS)	(98)
	Brief negative symptom scale (BNSS)	(99)
	Thought and language disorder (TALD)	(100)
	Frontal assessment battery (FAB)	(101)
	Bern psychopathology scale (BPS)	(102)
Motor scales	Neurological evaluation scale (NES)	(103)
	Bush Francis catatonia rating scale (BFCRS)	(104)
	Salpêtrière retardation rating scale (SRRS)	(105)
	Unified Parkinson’s disease rating scale (UPDRS)	(106)
	Abnormal involuntary movement scale (AIMS)	(107)
Behavioral tests	Postural knowledge test (PKT)	(79)
	Profile of nonverbal sensitivity (PONS)	(78)
	Coin rotation	(108)
	Test of Upper Limb Apraxia (TULIA)	(77)
Neuro- and social cognition	Mayer-Salovey-Caruso Emotional Intelligence Test (MSCEIT)	(109)
	Digit span backward (DSB)	(110)
	Test of nonverbal Intelligence (TONI)	(111)
	EMOREC-B	(56)
	Hinting task (HT)	(112)
	EmBODY tool	(113)
Functional assessments	Global assessment of functioning (GAF)	(88)
	Social and occupational functioning assessment score (SOFAS)	(114)
	Personal and social performance (PSP)	(114)
	University of California, San Diego performance-based skills assessment brief (UPSA-b)	(115)
	Social level of functioning (SLOF)	(116)

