**FIGURE 2 F2:**
[figure not shown]
Three fMRI gesture tasks—experimental setup. **(A) Gesture planning/performance task** with the modified Test of Upper Limb Apraxia (TULIA). Participants will be presented with 20 hand gestures in a random order (e.g., wave good-bye) and 10 control sentences with no gesture performance expected (e.g., “the airline flight is delayed”). Each trial will start with an instruction (3 s), followed by a triangle (planning phase: 3 s), then a 3–10 s interstimulus interval with a fixation cross (3–10 s), a circle (execution phase: 3 s), another 3–6 s interstimulus interval, and then a new gesture of the next trial is presented. **(B) Gesture perception task** with the modified Postural knowledge task (PKT). Each trial will start with a fixation cross (3–10 s) followed by a picture (max. 5 s) where the hand of the presented figure will be removed. Participants’ task is to choose the correct hand gesture provided below using button presses of a hand pad inside the scanner (1, 2, and 3) and respond while the picture is still displayed. In the example provided the correct gesture is number two. **(C) Gesture interpretation task** with point-light displays (PLD). Each trial will start with a fixation cross (3–10 s) followed by a PLD video, after which a question mark will be displayed (3 s). The video will include two PLD figures: one on the right side and the other on the left side of the screen. During the video, one PLD will perform a gesture while the other PLD will either follow or imitate these performed gestures. Participants’ task will be to indicate with the button press of a hand pad which of the two PLD figures (left or right) is imitating or following the gestures of the other when the question mark will be displayed. The gray connecting lines and the two gray circles (i.e., PLDs’ heads) are a visual aid and will not be present in the actual experiment.

Outcomes will be measured during four different time points: baseline, after cTBS (week 2), after SCRT (week 8) and follow-up (week 32) (see Table 3). At baseline, week 8 and week 32, the primary and all secondary outcomes will be tested. At week 2, the primary and a few secondary outcomes (i.e., nonverbal communication and clinical assessments) will be measured. Additionally, at baseline and week 8, neuroimaging data will be acquired to test the neural effects of the treatments.

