### Statistical Considerations and Plan

Assuming a medium effect size (*f* = 0.15) in a repeated measures ANOVA with moderate-high correlation between time points (0.75), a power of 0.95 and an alpha = 0.05, we will need 72 patients (24 per group). In addition, a control group of 24 healthy subjects will be required. All four groups will be compared pre-to-post with an interval of 8 weeks (see Figure 1). The main effects of the combined interventions on the primary and secondary outcomes will be calculated in a repeated measures design including 3 main time points (Baseline, week 2, and week 8) and three patient groups (A, B, and C). With the latest SPSS and R versions, we also will run additional (partial) correlations, linear regressions, MANCOVAS using covariates (e.g., age, education, and medication).

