### Limitations

This RCT entails a few limitations. First, we cannot eradicate the influence of medication; most patients suffering from schizophrenia are on antipsychotic treatment and other medication (e.g., blood pressure suppressants, antidepressants). However, for antipsychotic medication, we will control for Olanzapine equivalents in our statistical analyses. Second, we cannot eliminate gains linked to repeated test exposure as a result of retaking the same test under comparable conditions (i.e., retest effects). We counter these effects by randomizing the order of our test items for most of our assessments. Additionally, the time between most of our assessments makes training effects quite unlikely (i.e., 8 weeks, 32 weeks). Third, some of the data we collect are self-reports. Due to the subjective nature of self-reports, their psychometric aspects (e.g., reliability and validity) can be questionable or subject to biases (e.g., response bias). However, self-reports are necessary. For example, it is essential to compare patients’ subjective symptoms before and after intervention to find out if we are helping them. Fourth, another concern is the generalizability of the trial results. Participation in our study is only appropriate for a subgroup of schizophrenia patients, as it consists of 30 meetings in 3 months. As such, we can only include stable outpatients with good time management, commitment and tolerance to additional stress. This might cause the data collection to become arduous and dropout rates to be high.

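### The dose covariate is not limited to its pre-randomisation value, so the adjusted group comparisons may condition on something treatment can change

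*Protocol article*

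**What the plan says.** Four places in the protocol article bear on this.

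- Discussion, Advantages: "by collecting detailed demographic information over time, we will be able to correct for age, gender, education and antipsychotic medication dosage".
- Discussion, Limitations, after noting that the influence of medication cannot be removed: "for antipsychotic medication, we will control for Olanzapine equivalents in our statistical analyses". No model and no measurement time are given.
- Statistical Considerations and Plan, on the main analysis: a "repeated measures design including 3 main time points (Baseline, week 2, and week 8) and three patient groups (A, B, and C"). No covariate is named for it.
- The same section, next sentence: "we also will run additional (partial) correlations, linear regressions, MANCOVAS using covariates (e.g., age, education, and medication"). This is the only place where covariates are attached to named models.

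Medication history is assessed with the CASH (Behavioral and Clinical Assessments), and that sentence gives no time points. The eligibility criteria in Table 1 do not require a stable antipsychotic dose.

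**The concern.** Age, gender and education hardly change within a trial of this length. Of the four variables in the Advantages sentence, only dose can move materially, so the reference to collection over time has force mainly for dose. The Limitations sentence then promises control for dose without restriction.

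Dose after randomisation is not a baseline characteristic. The article itself makes a path from treatment to dose plausible. Its introduction reports fewer symptoms and relapses with the therapy on which the SCRT is based, and patients whose symptoms change may have their medication changed. Conditioning on such a dose can do two things:

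- remove the part of the treatment effect that runs through dose;
- open a path through unmeasured change in illness that drives both dose and outcome.

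In either case the adjusted A–B, A–C or B–C difference no longer estimates what randomisation protects. The same applies to the psychopathology, motor and functional outcomes, where a link with dose is at least as plausible as for TULIA.

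**Working it through.** **1. The plan's own figure.** Inputs from Statistical Considerations and Plan: f = 0.15, correlation ρ = 0.75, power 0.95, α = 0.05, three groups (k = 3), three time points (m = 3). For the group-by-time interaction under sphericity:

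- λ = f²·N·m/(1 − ρ) = 0.0225 × 72 × 3 / 0.25 = 19.44
- df1 = (k − 1)(m − 1) = 4; df2 = (N − k)(m − 1) = 138
- power = 0.952, and 72 is the smallest multiple of 3 that reaches 0.95.

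The stated 72 is reproduced. The calculation uses no covariate, so restricting the dose covariate does not change it.

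**2. What adjusting for later dose does.** In a linear model, let a be the effect of treatment on later dose and b the coefficient of later dose in the adjusted outcome model. Then:

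adjusted difference = total effect − a·b

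The document gives neither a nor b. The values below are assumptions, in roughly SD units: direct effect 0.40; treatment lowers dose by 0.2 or 0.4; dose acts on outcome with slope −0.3 or not at all. Where an unmeasured change in illness is present, it enters dose with weight 0.5 and outcome with weight −0.5, and dose has independent noise of SD 0.5. That shared cause adds −(0.5 × 0.5)/(0.5² + 0.5²) = −0.25/0.50 = −0.5 to b.

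| Assumed situation | a | b | True total | Adjusted for baseline and later dose |
|---|---|---|---|---|
| Treatment does not move dose | 0 | any | 0.40 | 0.40 |
| Treatment moves dose; dose unrelated to outcome | −0.2 to −0.4 | 0 | 0.40 | 0.40 |
| Dose is on the path to outcome | −0.2 to −0.4 | −0.3 | 0.46 to 0.52 | 0.40 |
| Illness change drives dose and outcome | −0.2 to −0.4 | −0.5 | 0.40 | 0.30 to 0.20 |
| Both | −0.2 to −0.4 | −0.8 | 0.46 to 0.52 | 0.30 to 0.20 |

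A simulation of 400,000 patients under the same assumptions agreed with every row to within 0.005. Adjusting for baseline dose alone recovered the true total each time. The bias is zero in the first two rows and otherwise takes the sign of −a·b. If treatment raised dose with b negative, the adjusted difference would be too large instead of too small.

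**3. Baseline TULIA in the main model.** With equal variance σ² at each time and ρ = 0.75, the per-patient variance entering the week-8 group contrast is:

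- baseline as a response (change from baseline): 2(1 − 0.75)σ² = 0.50σ²
- baseline as a covariate: (1 − 0.75²)σ² = 0.4375σ²

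The reduction is (0.50 − 0.4375)/0.50 = 12.5%. With 24 per group, the standard error of a pairwise contrast goes from √(2 × 0.50/24) = 0.204σ to √(2 × 0.4375/24) = 0.191σ.

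**The case against.** The strongest reply is that the article never says a week-2, week-8 or week-32 dose enters a treatment comparison. The Advantages sentence is loose Discussion prose: it files dose under demographic information and says what the authors will be able to do. The timing of a covariate is also something an article may leave to an analysis plan that is not shown. This stands in part. It rules out saying that the plan does condition on later dose. It does not remove the point, because the text is not simply silent: it ties the correction to information gathered over time and promises control for dose without limit.

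Several stronger readings are tempting and are not supported.

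- **That the primary analysis is compromised.** The main model is described without covariates. The Limitations wording is broad but names no model.
- **That doses do change, and over 32 weeks.** No dose change is reported. Limitations speaks of stable outpatients, although that is not a dose criterion. The main model ends at week 8.
- **That a given share of the A–B effect would be lost.** The article states no A–B difference, only f = 0.15. Converting that to a pairwise difference needs an assumed pattern of means, and any dose shift or slope would be invented.
- **That baseline TULIA has been overlooked.** It is already the first repeated measure in the main model, and the covariate list is only exemplary. Moving it to the covariate side is a gain in precision and does not correct an error.

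**Conclusion.** The point holds as a matter of wording that should be closed. As written, the plan permits adjustment of group comparisons for a dose measured after randomisation. Where that is done, the result is not the randomised effect if two conditions are both met: treatment changes dose, and dose affects or shares causes with the outcome. If either fails there is no bias. Neither can be judged from the document, so no size or direction can be given; the figures in the table are illustrations under stated assumptions.

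The dose concern is confined to the covariate-adjusted analyses. The separate gain of 12.5% in the variance of the week-8 contrast rests on the plan's own correlation of 0.75, read as the within-group correlation between baseline and week 8, and on equal variances. The sample size of 72 and its power of 0.952 are untouched.

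**What to change.** - State that treatment comparisons adjust only for pre-randomisation values: baseline olanzapine equivalents, age, gender and education. Table 3 marks allocation in the screening window and baseline at week 0, so name the visit that supplies the dose value.
- State that later dose is reported descriptively by arm, or used only in analyses labelled exploratory and not presented as estimates of the total treatment effect.
- In the main model, enter baseline TULIA as a covariate, with week 2 and week 8 as the responses.
- Reword the Advantages and Limitations sentences to match.

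The cost is a few sentences in the analysis plan. No extra patients are needed, and no extra data provided that the medication assessment already records a pre-randomisation dose. The aim of accounting for medication is still met.
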